## Methods

### Ethical Considerations

The study will strictly adhere to the principles outlined in the Declaration of Helsinki (World Medical Association; 2013). Before enrollment in this trial, all participants will be required to provide informed consent by signing a consent form. The protocol has undergone rigorous ethical review and received approval from the institutional ethics committee of the National Ayurveda Research Institute for Panchakarma (NARIP), Cheruthuruthy, Thrissur, Kerala, Peripheral Institute of CCRAS, Ministry of Ayush, Government of India and Scientific Review Board, Amrita Institute of Medical Sciences, Kochi (F.No.8/16/2023/NARIP/Tech meeting/2508 dated March 31, 2023), and the study is registered with the Clinical Trials Registry – India. The participants will be given incidental support charges of INR 100 (US $1.11) per visit as participant compensation. The trial is covered by clinical trial insurance for any incidents, and the participants will receive appropriate compensation if these arise.

Protocol amendments, if any are needed in the course of the trial, will be communicated to the institutional ethics committees at Amrita Institute of Medical Sciences, Kochi, and NARIP, Cheruthuruthy, India. Personal information about potential and enrolled participants will be collected, shared, and maintained in a confidential manner before, during, and after the trial unless subjected to judiciary (ie, court-related) disputes. Access to trial data will be granted only to the research team involved at NARIP and the Amrita Institute of Medical Sciences (AIMS). There will be no public access to the trial dataset. Dissemination policy includes publication of study findings in peer-reviewed indexed international journals.

### Eligibility Criteria

Apparently healthy volunteers aged 20 to 40 years who are physically independent, ambulatory, and right-handed; have a BMI of 18.5 to 24.9 kg/m^2^; and are willing to participate and provide written informed consent will be included in the study. Only those who agree to abstain from beverages such as coffee, tea, energy drinks, or other stimulants beginning 12 hours before undergoing fMRI will be considered for recruitment. The healthy status of volunteers will be confirmed through the absence of any active or chronic disease, as determined through a comprehensive medical evaluation that will include a detailed medical history, complete physical examination (including vital signs), 12-lead electrocardiogram, hematology, blood chemistry, serology, psychological assessment, and urinalysis, among other tests.

Individuals with any disease or symptom, with a history of psychiatric disorders as assessed using the Mini-International Neuropsychiatric Interview, with psychosomatic disorders, who used psychotropic medications known to interfere with the dopaminergic system or sedatives within the previous 6 months, with a family history of psychiatric diseases, with past or current abuse of psychoactive drugs, or who use alcohol or smoke will be excluded. Individuals contraindicated for magnetic resonance imaging (MRI), such as those with medical implants, retained wires (eg, temporary pacing), an increased risk of myocardial infarction or other cardiac problems, known pregnancy, nausea (due to aspiration risk), metallic dental work, cochlear implants, body jewelry, and other metallic foreign objects implanted in the body will not be eligible either. Individuals with cognitive impairment, women in the menstrual phase, those with intracranial abnormalities that could adversely affect the interpretation of brain scans, and those who self-identify as claustrophobic are also not eligible for participation in the study. In addition to this, participants deemed unfit for *nasya karma* therapy [10], such as those with fever, rhinitis, cough, or other inflammatory conditions as indicated in the Ayurveda treatises, will be excluded.

### Interventions

The participants in the intervention group will be administered *nasya karma* (nasal instillation) with *anu taila* at a dose of 3 mL per nostril for 7 days (on every alternate day for 14 days) as indicated in the Ayurveda treatises for healthy individuals. Before *nasya*, local oleation and sudation of the head region will be conducted for approximately 10 minutes. Following the *nasya karma* procedure, participants will inhale medicated smoke and rinse their mouths with lukewarm water. The control group, consisting also of healthy individuals, will not undergo any interventions to facilitate assessment of the specific effects attributed to *nasya karma* in the intervention group when compared to baseline measures in healthy individuals.

*Nasya karma* will be administered by the investigator at the hospital’s *panchakarma* unit except on assessment days, when it will be conducted at AIMS. Each participant will be closely monitored for 30 minutes following the procedure to observe any immediate effects or reactions. Vital signs such as heart rate, blood pressure, and respiratory rate will be monitored and recorded before and after every session. Participants reporting any adverse symptoms experienced after each session will be recorded through a standardized format designed to capture a wide range of potential side effects, including nasal irritation, headache, dizziness, nausea, or any other discomfort. Any serious adverse event will be reported immediately to the institutional ethics committee, and a causality assessment will also be conducted. Appropriate care will be provided for all adverse events requiring medical intervention, and they will be followed up on until resolution or stabilization.

If a participant experiences significant adverse effects, such as severe nasal irritation, fever, sinusitis, or any other serious discomfort that impacts their well-being, the intervention will be immediately halted, and the participant will be withdrawn. Discontinuation will also occur in cases of noncompliance with the treatment regimen, if the participant wishes to withdraw for any reason, or if the participant meets any of the exclusion criteria during the study. As the trial involves healthy volunteers, administration of concomitant medication is prohibited during the trial period of 30 days.

This study is structured as an exploratory randomized controlled clinical trial, with participants allocated in a 1:1 ratio to the intervention and control groups, matched for age and sex to comprehensively assess and evaluate the neurophysiological and holistic health effects of the *marsha nasya karma* procedure in comparison to a control group (Figure 1). Settings of the study include NARIP and AIMS.

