**Conclusions:**

This study will investigate the neurophysiological mechanisms of *nasya karma* by examining clinical, neuropsychological, and neuroimaging variables to identify associated neural patterns to develop therapeutic protocols for many diseases. The findings will also provide evidence for future research supporting the use of *nasya karma* as a practical and noninvasive therapeutic modality for treating cerebrovascular, behavioral, and neurological disorders as indicated in Ayurveda. The study will propel innovative research focusing on the neural mechanisms responsible for the delivery of central nervous system therapeutics to the brain, thereby bypassing the blood-brain barrier and yielding favorable outcomes in central nervous system diseases.

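### Routine recording of non-serious adverse symptoms is tied to nasya sessions, with no equivalent stated for controls or for either arm from day 14 to day 30

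*Protocol article*

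**What the plan says.** The Interventions section sets out routine safety capture in three parts, each timed by a nasya session:

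- Observation: "Each participant will be closely monitored for 30 minutes following the procedure to observe any immediate effects or reactions".
- Vital signs: these "will be monitored and recorded before and after every session".
- Symptoms: "Participants reporting any adverse symptoms experienced after each session will be recorded through a standardized format". The listed items are nasal irritation, headache, dizziness, nausea and any other discomfort.

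The same section contains provisions that are not tied to an arm, a session or a day. One reads "Any serious adverse event will be reported immediately to the institutional ethics committee", with a causality assessment. For adverse events that need medical care, "they will be followed up on until resolution or stabilization". A participant who comes to meet an exclusion criterion is discontinued.

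The control group receives no intervention. The section also fixes how long each participant is in the trial, since "concomitant medication is prohibited during the trial period of 30 days".

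Table 1 places the intervention on days 1 to 13, fMRI for both groups on days 1 and 14, and clinical assessment for both groups on day 30. It has no adverse-event row.

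**The concern.** The rule for non-serious symptoms hangs on an event that only one arm experiences and that stops before the halfway point of the trial period. Staff who follow the text will complete the form for nasya participants up to the last session. They are given no occasion to complete it for a control, or for anyone afterwards.

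What is at stake is whether the symptom counts can be interpreted. Most items on the form are non-specific. A headache or a dizzy spell in a nasya participant may or may not have anything to do with nasya, and the randomised control is the natural means of telling. The Interventions section itself justifies the untreated group as a way to isolate effects attributable to the procedure. If controls are not asked the same questions, that group cannot serve this purpose for tolerability. Symptoms that begin after the last session would enter the record only if they were serious or needed medical care, or if the participant volunteered them.

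**Working it through.** No sample size, power or alpha figure bears on this point, so the check is a comparison of sections plus a count of days.

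**1. When the session rule applies.** Inputs: 7 treatment days on alternate days over 14 days (Interventions) and an intervention period of days 1 to 13 (Table 1). Starting on day 1, the sessions fall on days 1, 3, 5, 7, 9, 11 and 13. That is 7 sessions, so the two places agree and the last session is on day 13.

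**2. What is left uncovered.** Input: a 30-day trial period (Interventions).

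- Nasya arm: 30 − 13 = 17 days (days 14 to 30 inclusive), and 17/30 = 57%.
- Control arm: 0 sessions, so 0 of 30 days are covered by the rule.

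**3. Whether another section fills the gap.**

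| Place | What it lists | Routine symptom collection in controls, or after day 13? |
|---|---|---|
| Interventions | Session-timed monitoring, vital signs and symptom form; arm-neutral rules for serious events, events needing care, and discontinuation | Not stated for non-serious symptoms |
| Data Management | Screening, recruitment and baseline data, nasya procedure assessments, laboratory reports, scales | The only item that plainly fits adverse symptoms is the nasya procedure assessment |
| Protocol Adherence Monitoring | Supervised sessions with immediate monitoring for adverse effects | Session-linked |
| Table 1, day 14 | fMRI, both groups | Not stated |
| Table 1, day 30 | Clinical assessment, both groups; the Abstract gives its content as sleep, well-being, cognition and quality of life | Not stated |

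**4. Whether contacts exist that could carry the form.** They do. Both arms are scanned on days 1 and 14 and assessed on day 30. No new visit is needed.

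**5. Precision, for scale only.** With 30 participants per arm, zero events of a given type gives a one-sided 95% upper limit of 1 − 0.05^(1/30) = 0.095, or 9.5%. A by-arm report would therefore be descriptive, which is why the interval should accompany each count.

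**The case against.** The strongest reply is that this is a journal article. The standardized format is not reproduced, and the full protocol may put it to controls and extend it to day 30. Table 1 is weak evidence of absence: it has no safety row even for the sessions at which the text requires recording, and it omits the day-1 clinical assessment that the Abstract schedules. The article also states no safety objective and describes its focus as mechanistic, so no planned comparison fails.

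Much of that stands. It limits the confidence and the weight of the point, and Table 1 alone would not carry it. It does not remove the point, because the article is not simply silent. It states a collection rule and anchors that rule to something controls never have.

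A reader might infer several stronger things that the documents do not support:

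- **That controls yield no safety data.** Serious adverse event reporting, follow-up of events needing care and discontinuation on exclusion criteria are not restricted to the nasya arm.
- **That nothing at all is collected from day 14 to day 30.** Both arms are seen on day 14 and day 30. What is missing is a stated symptom question at those contacts.
- **That symptoms count only within the 30-minute watch.** That watch is a separate sentence about immediate reactions. The symptom sentence has no time limit, so a symptom arising between sessions can be recorded at the next one, up to day 13.
- **That the named harms appear late.** The text gives grounds for halting treatment, "such as severe nasal irritation, fever, sinusitis, or any other serious discomfort that impacts their well-being", and says nothing about when they arise.
- **That the trial fails a stated safety aim.** The Abstract looks ahead to nasya "as a practical and noninvasive therapeutic modality for treating cerebrovascular, behavioral, and neurological disorders", but as evidence for future research, not as an objective of this trial.

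**Conclusion.** The point holds in a limited form. As described, routine recording of non-serious symptoms and vital signs is session-linked. It reaches no day in controls and, in the nasya arm, stops at day 13, leaving 17 of 30 days (57%) with no stated collection. Provisions for serious events, events needing care and discontinuation do cover all participants. The consequence is that non-specific symptoms would be counted in one arm only, with no like-for-like comparison.

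This rests on two assumptions. The first is that the full protocol adds no symptom collection beyond what the article describes, which the article alone cannot settle. The second is that day 30 is counted from day 1, as Table 1 lays it out; the Secondary Outcome Measures wording could be read as counting from the therapy, which would lengthen the gap. The documents give no background symptom rate, so the number of events that would be missed or misattributed cannot be estimated.

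It is a worthwhile and inexpensive improvement. It does not threaten the primary outcome or any planned analysis.

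**What to change.** - Use the existing standardized symptom form in both arms at the day 1, day 14 and day 30 contacts. Ask about the interval since the last of these shared contacts, so that the recall period is the same in each arm. Day 1, before the first session, serves as baseline.
- Keep the session records in the nasya arm, but base the between-arm summary on the shared contacts. Otherwise the extra occasions for reporting would inflate that arm's count.
- Add an adverse-event row to Table 1 for both groups through day 30.
- Report the proportion with each event descriptively by randomised arm, with confidence intervals.

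If the full protocol already does this, one sentence in the Interventions section and the Table 1 row are enough.

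The cost is a few minutes per visit at contacts already scheduled, and more minor events to record. Participants know their allocation, so some difference in reporting between arms will remain. The change concerns data collection only and leaves treatment and the rules for halting it untouched.

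### The on-study discontinuation rule also catches menstruation, because that exclusion criterion is not limited to entry or scan days

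*Protocol article*

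**What the plan says.** Two statements in the protocol article have to be read together.

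- **Interventions.** Discontinuation is mandatory in several cases, one of them "if the participant meets any of the exclusion criteria during the study". The clause covers every criterion and names no exception.
- **Eligibility Criteria.** The list of those who may not take part includes "Individuals with cognitive impairment, women in the menstrual phase". No time point is attached.

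The rest of the design sets the exposure to this rule. Volunteers are aged 20 to 40, and the arms are to be matched on age and sex, so women are evidently expected. Nasya is given in seven alternate-day sessions over 14 days, the last fMRI is on day 14, and clinical scales are assessed on day 30. The same section fixes the overall length: "administration of concomitant medication is prohibited during the trial period of 30 days".

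Nothing in the article times day 1 to the cycle, allows a session to be paused or a scan to be moved for menses, or says that the criterion lapses after entry.

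**The concern.** Most of the exclusion criteria are stable (implants, family history) or would rarely arise anew within a month (pregnancy). Menstruation differs: in this age range it normally recurs within about the length of the trial. A catch-all that would be harmless for the other criteria therefore becomes a scheduled trigger for this one.

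The consequence depends on what discontinuation means, and both meanings cost something.

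- **Leaving the study.** This is the more natural reading. The preceding sentence, on significant adverse effects, says "the intervention will be immediately halted, and the participant will be withdrawn", and a control participant has nothing to stop: "The control group, consisting also of healthy individuals, will not undergo any interventions". Day-14 scans and day-30 assessments would be lost in both arms. The Power Analysis is stated for 30 per group, the Sample Size section says that recruiting more volunteers may be difficult, and a modified intention-to-treat analysis cannot supply scans that were never taken.
- **Stopping nasya only.** The scans are kept, but affected women in the intervention arm receive a shortened course. The second component of the primary outcome is defined as the response after the full seven sessions.

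**Working it through.** The article gives no dropout rate, share of women or cycle data, so there is no stated figure to reproduce. The aim is to see how far the literal rule could reach.

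**Inputs from the article:** 30 per arm; last scan on day 14; trial period 30 days; seven alternate-day sessions, taken here as days 1, 3, 5, 7, 9, 11 and 13.

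**Assumptions (not in the article):** cycle length L of 28–30 days, with 35 as a long case; M = 4–6 menstrual days; share of women f = 25%, 50% or 75% in each arm.

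**Step 1. Share of menstruating women who meet the rule.** If day 1 is equally likely to be any of the L − M non-menstrual days, the probability of onset on days 2 to D is min(1, (D − 1)/(L − M)).

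| | L = 28–30 | L = 35 |
|---|---|---|
| Days 2–13 | 12/26 to 12/22 = 46–55% | 12/31 to 12/29 = 39–41% |
| Days 2–14 | 13/26 to 13/22 = 50–59% | 13/31 to 13/29 = 42–45% |
| Days 2–30 | 100% | 29/31 to 29/29 = 94–100% |

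With wider assumptions (L = 24–35, M = 3–7) the share for days 2–14 is 13/32 to 13/17, or 41–76%, and by day 30 it is at least 29/32 = 91%.

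**Step 2. Favourable entry timing.** If day 1 is the first day after menses, the next onset is on study day L − M + 1. For L = 28–30 that is day 23 (28 − 6 + 1) to day 27 (30 − 4 + 1): none by day 14, all by day 30. For L = 35 it is day 30 to day 32, so some women with long cycles would finish unaffected.

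**Step 3. If discontinuation means leaving the study.** With random entry and L = 28–30, the loss p runs from 0.462 (days 2–13) to 0.591 (days 2–14). The number remaining per arm is n = 30(1 − f·p), and the standard error is multiplied by √(30/n).

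| Share of women | Remaining of 30 per arm at day 14 | Standard error ratio |
|---|---|---|
| 25% | 26.5 to 25.6 | 1.06 to 1.08 |
| 50% | 23.1 to 21.1 | 1.14 to 1.19 |
| 75% | 19.6 to 16.7 | 1.24 to 1.34 |

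For L = 35 and 50% women, 24.2 to 23.3 remain and the ratio is about 1.11 to 1.14.

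**Step 4. If it means stopping nasya only.** Sessions received before an onset on days 2, 3, …, 13 are 1, 1, 2, 2, 3, 3, 4, 4, 5, 5, 6, 6. The mean is 42/12 = 3.5 of 7. At 50% women and L = 28–30, 15 × 0.462 = 6.9 to 15 × 0.545 = 8.2 of the 30 intervention participants are affected. They lose 24.2 to 28.6 of the 210 planned sessions (30 × 7), or 12–14%.

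**Step 5. If the criterion applied only at entry and on scan days.** Menses would force no discontinuation. With random entry, the share menstruating on day 14 is M/(L − M): 4/26 to 6/22 = 15–27%, or 4/31 to 6/29 = 13–21% for L = 35. These women would need the scan moved.

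**The case against.** The best reply is that the catch-all was never meant for passing states. The Interventions section expects nasal irritation, headache, dizziness and nausea after sessions and provides for recording them; withdrawal is for significant effects. Yet nausea and "Individuals with any disease or symptom" are themselves on the exclusion list. The authors evidently did not intend each listed state to end participation, and the menstrual criterion stands in the same sentence as conditions that matter for scanning. This carries weight: the likely intent is an entry or scan-day condition. It does not cure the text. For side effects the article gives a separate rule that points to the milder reading; for menses it gives none, and the clause runs throughout the study.

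A second reply is that a journal article leaves visit windows and the operational meaning of discontinuation to the full protocol. That is fair, and their absence is not the complaint. The complaint is that two rules the article does state combine badly.

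A third is that the day-14 figures rest on random entry. This stands. Because menses bar entry, a woman deferred for that reason may well start soon afterwards, and then nobody is affected by day 14. The high day-30 figure touches only the secondary scales, since fMRI ends on day 14.

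A reader might also infer that the two primary components would be measured in different mixes of men and women. Little follows from that, because the article plans no comparison of the two components.

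**Conclusion.** The point holds as a fault in the wording of a rule. Followed literally, the protocol discontinues women at their next menses. By day 14 this affects from none to roughly half or more of menstruating women, depending on where day 1 falls in the cycle, and nearly all by day 30. Under random entry with half of each arm women and 28–30-day cycles, about 21–23 of 30 per arm would remain for the day-14 scan, with a standard error 14–19% larger. If only nasya stops, affected women would average half the course. These sizes depend on assumed cycle length, menstrual duration, share of women and entry timing, none of which the article gives.

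Two stronger readings are not supported. A reader might infer that the trial will lose half its women before day 14; the article fixes neither the entry timing nor the share of women, and staff may apply the criterion only on scan days. A reader might also infer a biased comparison; the rule covers both arms and its trigger has no evident link to allocation, so the loss is one of precision, or of exposure in the intervention arm. Whether fewer sessions would mean a smaller BOLD response is not established by the article.

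**What to change.** Three changes of wording are enough.

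1. Apply the menstrual-phase criterion only at entry and on scan days. Preferably time day 1 soon after menses, so that day 14 falls before the next; otherwise move the scan by a few days.
2. Exempt this criterion from the on-study discontinuation rule.
3. State that participants who stop nasya for any reason, but have not withdrawn consent and can be scanned safely, still have the day-14 scan and the day-30 assessments and are analysed as randomised.

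Pausing and resuming sessions, or listing the safety criteria that do trigger stopping, are options for the sponsor rather than needed corrections.

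**Cost.** A protocol amendment of a few sentences. Without timed entry, about 15–27% of menstruating women (13–21% with 35-day cycles) would need a shifted day-14 scan, which lengthens the gap after their last session. Keeping participants who stopped nasya in the analysis may dilute the estimated effect slightly.
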